## Abstract

**Background:**

Esophagectomy is a highly complex surgical procedure, and it is associated with significant morbidity and mortality. The postoperative complication rate is high, with pneumonia being the most common. These are thought to arise from (micro-)aspiration of bacteria residing in the oropharyngeal and gastrointestinal (GI) tract. Selective decontamination of the digestive tract (SDD) is a prophylactic antibiotic strategy aimed at preventing these infections. SDD decolonizes the oropharyngeal and GI tract from pathogenic aerobic gram-negative rods, fungi and yeasts, while anaerobic, protective microbiota are preserved. The PERSuaDER trial aims to evaluate whether perioperative SDD can reduce postoperative pneumonia after esophagectomy.

**Methods:**

The PERSuaDER-trial is a randomized, controlled, open-label, superiority, multicenter, pragmatic, group-sequential trial aiming to include 854 patients with primary resectable esophageal carcinoma ((y)cT1-4a N0-3 M0) scheduled for transthoracic esophagectomy. The intervention group will receive SDD prophylaxis in addition to the standard care regimen. The SDD treatment comprises two oral liquids: an oral suspension containing amphotericin B and an oral solution containing both colistin sulfate and tobramycin. Participants are required to swallow the SDD suspension four times a day for 1 week, starting 3 days prior to the surgical procedure, with two doses on the day of surgery. All other aspects of care are identical to those provided to the control group (standard care without SDD). Participants will be asked to keep a diary and fill out quality of life, medical consumption, and productivity cost questionnaires. Interim analyses will take place after 30% and 60% of the participants have completed follow-up of 30 days after surgery, and after completion or termination of the trial.

**Discussion:**

It is hypothesized that the addition of SDD to the standard peri-operative care in esophageal cancer surgery will result in a reduction in the incidence of postoperative pneumonia. Furthermore, the trial will evaluate the impact of SDD on postoperative (infectious) complications and quality of life, and its cost-effectiveness.

**Trial registration:**

The PERSuaDER trial is registered in ClinicalTrials.gov (NCT05865743) and the European Clinical Trials Information System (CTIS) (EU Trial number: 2023-504144-33), Trial authorization date: 25.03.2024, protocol version 1.1, date: 03.03.2024.

## Administrative information

Note: the numbers in curly brackets in this protocol refer to SPIRIT checklist item numbers. The order of the items has been modified to group similar items (see http://www.equator-network.org/reporting-guidelines/spirit-2013-statement-defining-standard-protocol-items-for-clinical-trials/).

## Introduction

### Background and rationale {6a}

The incidence of esophageal carcinoma has increased considerably within the last thirty years worldwide and is expected to keep on rising [1, 2]. This change will likely lead to an increase in the number of esophagectomies that will be performed. Despite the implementation of minimally invasive surgical techniques, these surgeries are regularly accompanied by infectious complications, with postoperative pneumonia being among the most common (up to 40%) and anastomotic leakage (10–20%) the most dreaded [3–6]. These complications lead to an increase in hospitalization time, healthcare costs, and decreased long-term survival [7–9].

Postoperative pneumoniae are thought to arise from (micro-)aspiration of bacteria residing in the oropharyngeal and gastrointestinal (GI) tract [10]. Besides causing respiratory infections, these pathogens might also be able to induce local inflammation and abscess formation at the level of the esophago-enteric anastomosis, resulting in anastomotic dehiscence and eventually anastomotic leakage [11]. Therefore, it is hypothesized that eliminating these pathogens prior to surgery and during recovery potentially decreases the risk of postoperative infections and subsequent anastomotic leakage.

Aiming to prevent postoperative complications, some hospitals in the Netherlands already use a perioperative prophylactic antibiotic strategy that reduces GI colonization with aerobic gram-negative rods and yeasts, while preserving anaerobic microbiota [12]. This strategy, named selective decontamination of the digestive tract (SDD), consists of three oral, non-absorbable antimicrobial agents (colistin, tobramycin, and amphotericin B) that are administered four times daily as an enteral suspension [13]. SDD is associated with a reduced risk of ventilator-associated pneumonia in intensive care unit (ICU) patients [14].

A recent retrospective cohort study including 496 patients undergoing esophagectomy, showed that perioperative application of SDD was associated with a reduction in postoperative pneumonia (36.9% vs 20.1%, adjusted odds ratio (OR) 0.40 (0.23–0.67)) and anastomotic leakage (19.9% vs. 10.6%, adjusted OR 0.46 (0.26–0.84)) following esophageal surgery [15]. However, to date, prospective evidence supporting the use of SDD in the prevention of postoperative pneumonia after esophageal surgery is limited [16–20]. By evaluating the effect of SDD on infectious complications after esophagectomy, the PERSuaDER-trial aims to establish the evidence to implement SDD into the perioperative care of esophageal cancer surgery.

### Objectives {7}

The primary objective of the PERSuaDER trial is to evaluate the effect of SDD on infectious complications after esophagectomy, focusing on the prevention of pneumonia. Based on the afore mentioned findings, the hypothesis is that SDD will decrease the rate of post-operative pneumonia by 40% [15]. Secondary objectives are to determine additional benefits such as reduction of other infectious complications including anastomotic leakage, quality of life during the recovery period and evaluation of the risks of SDD. To support broader implementation, patient diaries will be used to collect data on patient preference and adherence, which are critical factors for the broader implementation of SDD. Additionally, a cost-effectiveness analysis will be conducted.

### Trial design {8}

The PERSuaDER trial has been designed as an open-label, superiority, multicenter, binational, randomized controlled trial. Patients will be randomly allocated (1:1) to a control cohort receiving regular care or an intervention cohort, receiving standard care plus SDD. The trial can be classified as pragmatic, as it aims to estimate the effect of SDD under normal clinical conditions. Consequently, eligibility criteria are well aligned with intended use in daily practice, and a placebo will not be used (Fig. 1).

**Fig. 1 Fig1:**
[figure not shown]
Flowchart PERSuaDER-trial

## Methods: participants, interventions, and outcomes

### Study setting {9}

The study will be conducted in Dutch and Belgian hospitals, specialized in the surgical treatment of esophageal cancer. These centers comprise both academic medical centers and non-academic hospitals. A list of study sites can be obtained from https://persuadertrial.org/.

### Eligibility criteria {10}

All consecutive adult patients with primary resectable esophageal carcinoma planned to undergo transthoracic esophagectomy at one of the participating Dutch and Belgian centers will be asked to participate.

#### Inclusion criteria

To be eligible to participate in this study, a subject must meet all the following criteria. First, a patient must have a diagnosis of primary esophageal adenocarcinoma or squamous cell carcinoma (cT1b-4a, N0-3, M0). Second, the tumor must be located in the mid or distal esophagus or at the level of the gastroesophageal junction. Third, the patient must be scheduled to undergo transthoracic esophagectomy with curative intent and planned for esophageal reconstruction with a gastric conduit or jejunal interposition. Participants can be included with the intention of primary surgical care or within a peri-operative chemotherapy or neo-adjuvant chemoradiotherapy schedule. Lastly, the patient must be at least 18 years old and capable of providing written informed consent.

#### Exclusion criteria

Patients will be excluded if they are planned for salvage surgery or reconstruction with colonic interposition, or have undergone resectional upper GI surgery within 30 days before randomization. Furthermore, we exclude patients who are unable to understand the study information and study instructions and give informed consent, patients who are enrolled in a trial that would interact with the intervention, patients with a known allergy, sensitivity, or interaction to the investigational medicinal product, patients who have chronic renal failure (GFR < 15mls/s) or undergo renal replacement therapy, patients with pre-existing degenerative neuromuscular diseases, women of childbearing potential not using adequate contraception, patients who are known to be colonized with or have infections caused by microorganisms resistant to tobramycin or colistin or against carbapenems, and patients with the inability to swallow the SDD.

Patients will not be excluded on the basis of old age criteria, ASA (American Society of Anesthesiology) classification or Charlson Comorbidity Index. If patients are deemed fit for surgery, meet the inclusion criteria, and none of the exclusion criteria, they are eligible to participate in the study.

### Who will take informed consent? {26a}

The treating physician will approach all patients undergoing an esophagectomy for esophageal cancer about the possibility of participating in the PERSuaDER-trial. If the potential participant has consented to be contacted by members of the research team, they will be informed about the study, and additional information regarding the trial will be provided. After the patient has read the patient information brochure, any remaining questions will be answered. Once the patient decides having had sufficient time to consider his or her decision and all questions have been answered satisfactorily, the participant will subsequently be asked to return their signed consent in the provided return envelope. Once the signed informed consent forms are received, patients will be screened for the inclusion and exclusion criteria, randomized, followed by the distribution of questionnaires, a diary, and, if allocated to the intervention group, study medication.

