### Intervention description {11a}

#### SDD

Patients randomized towards the intervention arm will receive SDD medication with instructions from the hospital pharmacy or research staff. The SDD treatment comprises two oral liquids: an oral suspension (5 mL) containing amphotericin B (100 mg/mL), followed by an oral solution (another 5 mL) containing both colistin sulfate (20 mg/mL) and tobramycin (16 mg/mL). Patients are required to take the SDD four times a day for 1 week, starting 3 days prior to the surgery. On the day of surgery, intake is limited to an early morning and a late evening dose. Patients will be asked to hand in the empty vials of the SDD upon hospital admission to monitor therapy compliance and drug accountability. Patients in the control group will not receive a placebo.

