#### Questionnaires and diaries

Patients in both the intervention and control arms will be asked to keep a diary during the perioperative period. This allows us to explore potential side effects, therapy adherence and real-life experiences of patients. Quality of Life (QoL) will be measured by three validated questionnaires (EORTC OG25, QLQC30 and EuroQol-5D-5L) provided to patients 1 week before surgery, and at 30 days, 3 months, and 6 months postoperatively [23, 24]. We will estimate direct and indirect health-related costs with the help of a medical consumption and productivity cost questionnaire developed by the iMTA [25, 26]. These questionnaires will be provided to the participants together with the QoL questionnaires at 3 and 6 months postoperatively.

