#### Participant timeline {13}

Participant timeline is outlined in Table 1.

**Table 1 Tab1:** Schedule of assessments and study procedures

	Study period										
	**1–6 weeks until surgery**	**D-3**	**D-2**	**D-1**	**D0**	**D1**	**D2**	**D3**	**D30**	**D90**	**D180**
	Outpatient clinic	Home		Hospital					Home		
Screening study eligibility	x										
Advising pregnancy test if applicable	x										
Information on PERSuaDER, study content and consent	x										
Collection informed consent	x										
Randomization	x										
Dispersion and instruction on intervention medication	x										
SDD intervention		x	x	x	x	x	x	x			
Patient diary		x	x	x	x	x	x	x			
Resectional specimen swabs					x						
Pneumonia assessment									x	x	x
Other complications assessment*									x	x	x
Medication adherence assessment									x		
QoL questionnaires	x								x	x	x
Other secondary outcome assessment*									x	x	x
(S)AE, SUSAR assessment **		x	x	x	x	x	x	x	x	x	x

* Other secondary outcomes: postoperative length of stay, the intensive care unit (ICU) length of stay, re-admissions, cost assessment. ** As described in the “Adverse event reporting and harms {22}” section*. QoL*, Quality of Life; *(S)AE*, (Serious) Adverse Event; *SUSAR*, Suspected Unexpected Serious Adverse Event

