## Assignment of interventions: blinding

### Who will be blinded {17a}

As an open label study, allocation of the intervention will not be blinded. Analysis of the outcome parameters will be blinded.

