### Statistical methods

#### Statistical methods for primary and secondary outcomes {20a}

The primary analysis will be according to intention to treat, including all randomized participants. Per protocol analyses will be performed in patients that received SDD or no SDD in accordance with the randomized allocation. For the analysis of the primary outcome, we will use Cox regression (cause-specific hazard ratio which defines the effect on the daily hazard), with censoring for death and putative loss to follow-up, and we will adjust for the stratification variables by including these as strata in the regression. A sensitivity analysis will be performed using Fine and Gray regression (sub distribution hazard ratio which defines the effect on cumulative incidence) considering mortality as competing events and censoring for putative loss to follow-up, also including the stratification variables as strata.

Secondary outcomes will be analyzed using logistic regression (all-cause mortality and rate of re-operation), time-to-event analysis (incidence using Cox regression and cumulative incidence using Fine and Gray regression), or linear regression (length of stay and quality of life), as appropriate.

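### The only pre-surgery quality-of-life and EQ-5D-5L measurement is handed out after open-label randomization, so patients complete it knowing their arm

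*Protocol article*

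**What the plan says.** The order of procedures is in the protocol article, section {26a}. Signed consent is received, eligibility is checked, and patients are "randomized, followed by the distribution of questionnaires, a diary, and, if allocated to the intervention group, study medication".

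The section on questionnaires and diaries lists the EORTC OG25, the QLQ-C30 and the EQ-5D-5L, "provided to patients 1 week before surgery, and at 30 days, 3 months, and 6 months postoperatively". Table 1 marks the first QoL assessment in the column "1–6 weeks until surgery", which also holds consent and randomization. It shows no other QoL assessment before surgery.

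On blinding, section {17a} states "As an open label study, allocation of the intervention will not be blinded", and the intervention description adds "Patients in the control group will not receive a placebo". On treatment timing it states "Patients are required to take the SDD four times a day for 1 week, starting 3 days prior to the surgery".

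On analysis, section {20a} gives only "linear regression (length of stay and quality of life), as appropriate". The objectives section announces a cost-effectiveness analysis without describing how utilities enter it.

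**The concern.** A baseline protects a randomized comparison because allocation cannot have influenced it. That holds automatically for a measurement taken before randomization. For a self-reported measurement taken afterwards by an unblinded patient, it has to be assumed.

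Knowledge of the arm can act in two ways here. It can colour the answers, for example through reassurance at being given the prophylaxis or disappointment at not being given it. It can also change who returns the form, since one arm receives a medication package and instructions and the other does not.

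The protocol's discussion accepts that having no placebo raises the risk of biased outcome assessment. The mitigation it offers, objective criteria, concerns the primary endpoint and does nothing for patient-reported scores. At stake are the secondary QoL comparisons and, through the starting utility, the QALYs.

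**Working it through.** **Order of events.** The protocol states no figure that needs reproducing, so the first check sets the sections side by side.

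1. Section {26a}: consent, screening, randomization, then questionnaires.
2. Table 1: randomization and the first QoL form share one column. The table does not order events within a column, so it neither confirms nor contradicts step 1.
3. Questionnaire section: first set one week before surgery. Randomization falls one to six weeks before surgery, so the set comes at or after it.
4. Sections {17a} and {11a}: no blinding and no placebo, so the patient knows the arm.
5. Section {11a}: SDD starts three days before surgery. A form completed one week before surgery precedes the first dose, so the drug itself cannot affect it. Only knowledge of the arm can.

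No section contradicts this order, and none places a QoL form before allocation.

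**Scale, on assumed inputs.** The documents give no value for any quantity below.

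Let *d* be the shift between arms in the pre-surgery score caused by knowing the arm, *e* the corresponding reporting shift at follow-up, and *b* the slope of outcome on the pre-surgery score. The bias of the difference adjusted for the post-randomization score is *e* − *b*·*d*. With a pre-randomization baseline it is *e*.

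- Shift gone by follow-up (*e* = 0), with *d* from 0.05 to 0.20 SD and *b* from 0.3 to 0.7: the size runs from 0.3 × 0.05 = 0.015 SD to 0.7 × 0.20 = 0.14 SD, opposite in sign to *d*.
- Shift fully persistent (*e* = *d*): the bias is *d*(1 − *b*). With *d* = 0.20 and *b* = 0.5 this is 0.10 SD, against 0.20 SD with a pre-randomization baseline.

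**QALYs.** Take an assumed baseline utility shift of 0.01 to 0.05 and measurements from 7 days before surgery to day 180.

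- Unadjusted trapezoid: the baseline utility has weight 0.5 × 37/365.25 = 0.0507, giving 0.0005 to 0.0025 QALY.
- Adjusted for baseline: the horizon is 187/365.25 = 0.512 years. Take the slope of QALY on baseline utility as 0.3 to 0.7 times this, that is 0.154 to 0.358. The net effect is (0.0507 − 0.154) × 0.01 = −0.001 to (0.0507 − 0.358) × 0.05 = −0.015 QALY.

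**The case against.** The strongest reply is that the harm depends on an analysis choice the protocol does not make. A reader might infer from the order of procedures that the trial will adjust for a contaminated covariate, or that a contaminated starting utility is built into its QALYs. The documents do not support that: section {20a} names no baseline covariate or change score, and no section describes how the first EQ-5D-5L value is used. This stands, so the point is conditional on use. It is still the only pre-surgery value available for any such use.

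Second, one week before surgery is a reasoned time for a baseline: close to the operation, yet before the first dose. Patients may be on neoadjuvant chemoradiotherapy or perioperative chemotherapy schedules, so a form completed weeks earlier may describe a different state of health. This also stands. The choice is a trade-off, and the order of mailing is not the only thing in the way.

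Third, the same unblinded patients answer at 30 days, 3 months and 6 months. If the reporting shift persists, adjusting for a post-randomization score partly cancels it and a pre-randomization baseline does not. That is arithmetically correct, as shown above. But such cancellation depends on two unknown shifts happening to match, and the remaining bias is the ordinary open-label problem at follow-up, which the proposed change does not claim to solve.

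A reader might also see a conflict between the one-week timing and the Table 1 column. There is none, because the window of one to six weeks includes one week.

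**Conclusion.** The point holds as a minor improvement for secondary endpoints. Section {26a} states the order outright and nothing contradicts it: the only pre-surgery QoL and EQ-5D-5L set is completed after open-label allocation.

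Whether this biases anything depends on the set being used as a baseline, and on knowledge of the arm moving answers or return rates. Neither can be established from the protocol. The ranges of 0.015 to 0.14 SD and 0.001 to 0.015 QALY rest wholly on assumed shifts and slopes. The SD range and the adjusted QALY range also need the shift to be absent at follow-up. They show that any effect is probably small; they do not estimate it. The pneumonia endpoint is not touched.

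**What to change.** Change the order in section {26a}: give the first QoL and EQ-5D-5L set with the consent documents, have it completed after consent and before randomization within the Table 1 window, and use that set as the baseline. Amend the one-week timing in the questionnaire section to match.

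For patients already enrolled, or for everyone if the one-week measure is kept, label it as post-randomization. Add a sensitivity analysis of QoL and QALYs that does not adjust for it.

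Costs: 
- The baseline may lie up to about six weeks before surgery instead of one.
- Return of a form becomes a step before randomization, which is some burden in a pragmatic trial expecting to recruit about 35% of its source population.
- Some patients who prove ineligible will have completed a form, since screening follows consent.
- Recruitment has run since October 2024, so a change now produces two types of baseline that must be identified in the data.

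The sensitivity analysis alone needs no change in conduct and is the minimum.

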### Additional consent provisions for collection and use of participant data and biological specimens {26b}

The informed consent obtained from the participants will cover peri-operative data collection including the collection and analysis of the microbial swabs as part of an efficacy assessment of the intervention. Through additional questions participants are questioned for consent to share patient-reported outcome measures with the Prospective Observational Cohort Study of Oesophageal-gastric cancer Patients (POCOP) registry and to contact the participant for future studies.

### Interventions

#### Explanation for the choice of comparators {6b}

Patients will be informed that participation in the PERSuaDER trial means that they will either receive standard care without SDD or standard care with SDD.

### Intervention description {11a}

#### SDD

Patients randomized towards the intervention arm will receive SDD medication with instructions from the hospital pharmacy or research staff. The SDD treatment comprises two oral liquids: an oral suspension (5 mL) containing amphotericin B (100 mg/mL), followed by an oral solution (another 5 mL) containing both colistin sulfate (20 mg/mL) and tobramycin (16 mg/mL). Patients are required to take the SDD four times a day for 1 week, starting 3 days prior to the surgery. On the day of surgery, intake is limited to an early morning and a late evening dose. Patients will be asked to hand in the empty vials of the SDD upon hospital admission to monitor therapy compliance and drug accountability. Patients in the control group will not receive a placebo.

